### The healthy group

The healthy group will not take any treatment.

## Outcome evaluations

### Primary outcomes

Yale Comprehensive Tic Severity Scale (YGTSS) is the most commonly used scale to evaluate the severity of tic condition in clinic. The scale scores motor tic and vocal tic respectively, and clinicians score them by asking questions from the guardians and observing their performance in clinic. The total score of YGTSS in patients with TD, if it is less than a score of 25, it is considered as mild, a score of 25 to 50 is considered as moderate, and a score of 50 above is considered as severe.

### Secondary outcomes

#### Infrared image acquisition at the back along the governor vessel

Infrared images will be captured along the governor vessel of both groups of children: Healthy children and children with TD, aiming to identify any dissimilarities between these two groups. Additionally, infrared images will be captured in children with TD before and after the intervention, as for a comparative analysis.

#### Metabolomics

Fecal and urine samples will be collected from both groups of children: healthy children and children with TD. Through analysis and detection, biomarkers associated with acupuncture treatment in children with TD can be discovered. Additionally, the KEGG database will be utilized to analyze the metabolic pathways linked to these biomarkers in the acupuncture treatment of children with TD.

## Infrared thermography system capture

### Research instrument

The BK-MT02A digital medical infrared thermal imager, manufactured by Beijing Zhongrui Bokang Medical Equipment Co., Ltd., will be utilized to capture images of the spinal region.

### Testing requirements

The environment of the infrared thermography examination room is relatively stable, the temperature is maintained at 24 degrees Celsius, the relative humidity is less than 70%, the indoor air flows naturally, there is no wind and dust, and there is no direct heat source. Subjects should avoid drinking alcohol, coffee and other irritating foods 24 h before shooting, prohibit from eating too cold or overheated food 1 h before the shooting, avoid strong cold or overheated environment (such as direct blowing under air conditioning), and stop physical therapy and taking drugs 10 min before shooting and avoid leaning on object.

After entering the examination room, the subject should take off his/her shirt and expose the bare shooting area, remove necklaces and other accessories, and hair should not cover the forehead and neck, the subject is required to sit quietly and rest for 15 min to adapt to the ambient temperature, and avoid pressing or scratching the examination area during the rest period.

### Acupoint examination

The anatomical coordinates of the Dazhui, Zhiyang, Mingmen, Yaoyangguan, and Jinsuo points on the body surface were determined. To facilitate the localization of these acupoints during image acquisition without altering their local body surface temperature, a custom-made hollow foam adhesive cube, measuring 14 mm in inner diameter and 3 mm in height, is applied as an insulating marker on each acupoint.

### Testing process

During the shooting process, the subject keeps the body upright, facing the camera with both upper limbs hanging down on both sides of the body. The infrared camera lens is 1 m to 2 m away from the subject, and the professional technician will take the picture, collect the infrared thermogram of the spine area and save the infrared image. Within the Du meridian area, specific meridian points such as Dazhui, Zhiyang, Mingmen, Yaoyangguan, and Jingsuo, will be manually traced. Afterwards, the computer automatically measure the average temperature of this area, record as t, and document the inspection results.

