### Randomization

The subjects will be randomly assigned to two groups: the experimental group and the control group. There will be 30 cases in each group. Randomization was performed using the R software, generating a random number table with a block length of 4 and a distribution ratio of 1:1. Upon enrollment of eligible subjects, the randomizer allocated them to groups based on the order of their entry into the trial, labeling “1” as the experimental group and “2” as the control group. Throughout the trial, the acupuncturist will be aware of the patient’s group allocation. The subjects, evaluators of therapeutic effects, and individuals conducting the statistical analysts will be blinded to group allocation.

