## Processing of infrared thermographic images

The temperatures of specific acupoints (Dazhui, Zhiyang, Mingmen, Yaoyangguan, and tendon contraction) in the area of the Du meridian will be manually traced. Use SPSS 20.0 statistical software for analysis. Quantitative data is expressed as “mean ± standard deviation” (x ± s). If the data follows a normal distribution, paired sample t-test is used; if the data does not follow a normal distribution, non-parametric tests (Wilcoxon signed-rank test) are used. Skin temperature comparison before and after intervention at different acupoints in different groups is analyzed using one-way analysis of variance (ANOVA) if it follows a normal distribution and has equal variances. If the data follows a normal distribution but has unequal variances, Welch’s test is used. If the data does not follow a normal distribution, Kruskal-Wallis H test is used. *P* < 0.05 indicates statistical significance of the differences.

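### Thermography temperatures come from hand-traced areas not tied to the 14 mm marker, and no masking of the tracer to TD/healthy status or visit is stated

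*Protocol article*

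**What the plan says.** All references are to the protocol article.

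- **Region measured.** Testing process: "specific meridian points such as Dazhui, Zhiyang, Mingmen, Yaoyangguan, and Jingsuo, will be manually traced". The next step is "Afterwards, the computer automatically measure the average temperature of this area", and that mean is recorded as t. The section Processing of infrared thermographic images repeats the step for the analysed data: the acupoint temperatures "in the area of the Du meridian will be manually traced".
- **Marker.** Acupoint examination: "a custom-made hollow foam adhesive cube, measuring 14 mm in inner diameter and 3 mm in height, is applied as an insulating marker" at each of the five points. Its stated purpose is location: "To facilitate the localization of these acupoints during image acquisition without altering their local body surface temperature".
- **Masking.** Randomization: "The subjects, evaluators of therapeutic effects, and individuals conducting the statistical analysts will be blinded to group allocation". The two groups in that section are the experimental and control arms. The healthy children are not randomised.
- **Contrasts.** Secondary outcomes names two for thermography: healthy children against children with TD, and TD children before against after the intervention. The image-processing section adds a comparison of groups by ANOVA, Welch's test or Kruskal-Wallis.
- **Expectation.** The Introduction describes even heat along the governor vessel in healthy children and rising heat in TD. The Discussion says the unevenness improves clearly after acupuncture.
- **Safeguard.** Quality control promises standard operating procedures, computer-generated results and traceable images for thermography. It mentions neither tracing nor masking of the reader.

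**The concern.** The number analysed is a mean over an area whose edge a person draws. Whoever knows that an image comes from a child with TD, or from week 12, and knows the expected pattern, can place that edge slightly differently without intending to. The software average inherits the edge. A consistent difference in tracing between TD and healthy images, or between baseline and week-12 images, would appear as a temperature difference. A tracing area that varies at random would add noise.

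At stake is one of the two secondary outcomes. The TD-versus-healthy contrast also supports the article's aim of building a basis for diagnosing TD by thermography. The primary outcome, YGTSS, is not affected.

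**Working it through.** The plan states no figure on this point to reproduce. The check is mainly one of text.

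**1. Is the measured area fixed?** Testing process and the image-processing section both prescribe manual tracing. Neither gives a size, shape or rule, and neither mentions the marker. Acupoint examination gives the marker a fixed inner diameter but assigns it only the task of showing where the point is. Testing process also allows a camera distance of 1 m to 2 m, so with the same lens the 14 mm opening can differ about twofold in size between images. A traced outline has no constant physical area unless it is tied to the marker.

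**2. Which contrasts does the stated masking reach?**

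| Contrast | What the tracer would need to be masked to | Stated? |
|---|---|---|
| TD vs healthy | Disease status | No |
| Before vs after, in TD children | Visit | No |
| Change, acupuncture vs sham | Arm | Yes, if the tracer counts as an evaluator of therapeutic effect; the Randomization section does not say |

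In the third row, an expectation about visit alone would act about equally in both arms and largely cancel.

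**3. How much would a shift matter?** This is an illustration only. From the documents: 60 TD and 30 healthy children, 30 per arm, 20% dropout (30 × 0.8 = 24), test level 0.05. Assumed: temperature SD s (between children, or of the change) of 0.5 to 1.0 °C, and a systematic tracing shift b of 0.1 or 0.2 °C, with no true difference.

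Rejection rate = Φ(b/SE − 1.96) + Φ(−b/SE − 1.96).

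- TD vs healthy: SE = s·√(1/60 + 1/30) = 0.2236·s. For s = 0.5, SE = 0.112. With b = 0.1, b/SE = 0.894 and the rate is Φ(−1.07) + Φ(−2.85) ≈ 0.145.
- Before–after in one arm: SE = s/√n. For s = 0.5 and n = 30, SE = 0.091. With b = 0.1, b/SE = 1.095 and the rate is Φ(−0.86) + Φ(−3.06) ≈ 0.195.

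| | s = 0.5, b = 0.1 | s = 0.5, b = 0.2 | s = 1.0, b = 0.1 | s = 1.0, b = 0.2 |
|---|---|---|---|---|
| TD 60 vs healthy 30 | 14.5% | 43.2% | 7.3% | 14.5% |
| Paired, n = 30 | 19.5% | 59.1% | 8.5% | 19.5% |
| Paired, n = 24 | 16.5% | 50.0% | 7.8% | 16.5% |

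A consistent shift of 0.1 to 0.2 °C would matter under these assumptions. Whether tracing at or near a 14 mm marker can produce such a shift cannot be determined from the documents.

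**The case against.** - **The tracer may simply outline the marker opening.** This is a natural reading, because the marker and tracing sections follow one another and cover the same five points. The sections do not contradict each other. If this is the practice, the room for bias is small. It stands as a limit on size, but the article does not say it.
- **Standard operating procedures are promised, and the article condenses a fuller protocol.** Rules for drawing regions and coding images could sit there. But the article does more than stay silent: it states manual tracing twice as the method. A general promise of procedures does not replace that.
- **The numbers are assumed.** This stands in full. A uniform shift is also only a rough model of the expected pattern, which is a changed distribution of heat, and the 60-versus-30 two-sample test is a simplification of the tests listed.
- **The randomised comparison is protected.** Largely so, on the condition shown in the working.

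A reader might infer that the thermography findings will be falsely positive at a known rate, or that the comparison of acupuncture with sham is compromised. The documents support neither: they give no tracing error or SD, and evaluators are stated to be masked to arm.

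**Conclusion.** The point holds as a weakness in how a secondary outcome is measured. The plan prescribes a subjective step, does not tie it to the objective landmark it already places on each child, and states no masking to disease status or visit, while declaring the direction it expects. The TD-versus-healthy and before–after temperature contrasts are open to reader bias of unknown size. The percentages show only what a shift of 0.1 to 0.2 °C would do at an assumed SD of 0.5 to 1.0 °C; they do not estimate the bias in this trial. The conclusion assumes that no unshown procedure confines tracing to the opening or codes the images. It is worth correcting because the remedy is cheap and can still be applied: images are saved, and the Trial status section reports that recruitment is continuing.

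**What to change.** In Testing process and in Processing of infrared thermographic images, replace manual tracing with wording such as: *The region for each acupoint is a circle centred in the marker opening, scaled to the opening in each image and set just inside its edge so that no foam pixels are included; t is the mean temperature within it. Before regions are placed, all images are saved under random codes that hide TD/healthy status, arm and visit, and are processed in random order.*

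Scaling is needed because the camera distance varies from 1 m to 2 m. The inner margin keeps the insulating foam out of the mean.

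Cost: two sentences, a little file recoding and some re-processing. Images already stored can be re-read in the same way. No new visits or measurements on the children are needed. The article does not say whether the imager's software can place such a circle, so this should be confirmed first.

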The medical infrared imaging system (TTM) can detect the specific band of infrared signals of thermal radiation on the body surface, and convert the signal into images that can be distinguished by human vision, reflecting the thermal structure characteristics of the human body [16]. When a certain part/area of the body happened to be experience pathological changes, the part/area around it will first have changes in tissue metabolism that corresponding to certain pathological manifestation which reflected as abnormal temperature of the skin [17].The mediators involved in regulation of body temperature mainly include PGE2, Na+/Ca2+, corticotropin-releasing hormone (CRH), cyclic adenosine monophosphate (cAMP), NO, etc [18]. When there is a change of endogenous substances in the body, these mediators will be affected, reflected as a change in body temperature. Therefore, we hypothesize that children with TD with abnormal metabolites will also experiencing changes in body temperature. In the early stage of our research, we found that indeed there are differences in the structure of the infrared thermography along the governor vessel between healthy children and children with TD. The heat distribution along the governor vessel in healthy children appeared to be in a uniform state (Fig. 1), whereas in children with TD, the heat distribution along the governor vessel shows a tendency of rising/floating (Fig. 2).

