## Discussion

Currently, the clinical diagnosis of TIC disorder (TD) is primarily based on scale evaluation, which lacks of objective evaluation indicators and detection methods. However, there are metabolic differences in urine and feces between children with TD and healthy children. In order to further investigate the pathogenesis of TD, it is crucial to explore the urine and feces metabonomic analysis. In our preliminary study, our research discovered a distinct difference in the body temperature along the governor vessel between children with TD and healthy children: the heat distribution along the governor vessel of children with TD is in uneven state when compared to that of healthy children. Importantly, this uneven heat distribution is significantly improved after acupuncture treatment. Therefore, we hypothesize that this metabolic abnormality may be related to the changes of structure of infrared thermography of specific areas along the governor vessel and acupoints around it. Since currently, there is no effective diagnostic equipment for TD, so by fully utilizing the infrared thermal imaging technology and metabonomic analysis to further explore the underlying molecular mechanism by which changes of body temperature occur holds potential in identifying targets for future research purpose on the mechanism of acupuncture treatment aimed at regulating energy metabolism in children with TD.

This approach may also aid in the identification of micro-biomarkers associated with treatment outcomes and contribute to the development of a theoretical and experimental basis for diagnosing TD using infrared thermal imaging technology. However, this experiment has several limitations, including a small sample size, a long treatment cycle, low cooperation of children, and a potentially high dropout rate. Consequently, further studies with larger sample sizes, longer-term interventions, and comprehensive follow-up evaluations are needed.

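### The thermography hypothesis is a heat pattern along the governor vessel, but the plan records average temperatures and tests absolute acupoint values, so it can miss a redistribution or confuse it with overall skin warmth

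*Protocol article*

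**What the plan says.** **The hypothesis.** The Introduction says of healthy children that "The heat distribution along the governor vessel in healthy children appeared to be in a uniform state", and of children with TD that "the heat distribution along the governor vessel shows a tendency of rising/floating". The caption of Fig. 2 repeats the upward tendency. The Discussion says "the heat distribution along the governor vessel of children with TD is in uneven state when compared to that of healthy children" and adds that acupuncture improved this unevenness. The Abstract and the end of the Introduction accordingly name change in the structure of the thermogram as an outcome; the Abstract makes it secondary.

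**The measurement.** Acupoint examination places an insulating marker on each of five points. Under Testing process, "specific meridian points such as Dazhui, Zhiyang, Mingmen, Yaoyangguan, and Jingsuo, will be manually traced", and then: "Afterwards, the computer automatically measure the average temperature of this area, record as t".

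**The analysis.** Processing of infrared thermographic images again lists the five points (one appears under a translated name). It gives a paired t-test or Wilcoxon signed-rank test, and for "Skin temperature comparison before and after intervention at different acupoints in different groups" a one-way ANOVA, Welch or Kruskal-Wallis test. It defines no slope, upper-minus-lower difference, spread across points or other measure of evenness, and so no group comparison of one.

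**The concern.** The hypothesis concerns how heat is distributed within one child. The fixed variable and tests concern how warm an area or point is. These can diverge in both directions:

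- Heat can move from lower to upper points with little or no change in average temperature.
- A child's whole back can be warmer, so that every point reads higher, while the distribution stays perfectly even.

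The plan could therefore overlook a real redistribution, or report a general difference in skin temperature as a structural one. This affects both thermographic comparisons: acupuncture against sham after treatment, and TD against healthy children at baseline. The primary outcome, YGTSS, is not touched.

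**Working it through.** The article gives no SD, effect size or power for thermography, so there is no stated figure to reproduce. Its sample-size paragraph concerns an effectiveness rate.

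**Inputs from the article.** Five points; 30 children per randomised group; 60 TD and 30 healthy children at baseline; 20% dropout, hence 30 × 0.8 = 24 per randomised group; two-sided tests at 0.05.

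**Inputs assumed.** Between-child SD of a point temperature 0.8 °C (1.0 °C as a check); correlation r between two points in one child of 0.5 to 0.8; a shift of 0.25 °C.

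**Step 1: what an average can see.** Take five points from top to bottom, with illustrative temperatures.

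| Profile (°C) | Mean | Top minus bottom | SD across points |
|---|---|---|---|
| 33.00, 33.00, 33.00, 33.00, 33.00 | 33.0 | 0 | 0 |
| 33.50, 33.25, 33.00, 32.75, 32.50 | 33.0 | 1.0 | 0.40 |

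A single whole-area mean cannot tell these apart. Conversely, adding a constant to the first profile changes all five point readings and leaves the last two columns at 0.

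**Step 2: what per-point tests can see.** For one point, d = 0.25/0.8 = 0.3125. For the upper-minus-lower difference, the SD is 0.8 × √(2(1 − r)), which is 0.80 at r = 0.5 and 0.506 at r = 0.8. If the upper point warms by 0.25 °C and the lower cools by 0.25 °C, the difference shifts by 0.50 °C. If only the upper point warms, it shifts by 0.25 °C. Power is from the noncentral t distribution.

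| Quantity tested, SD 0.8 °C | d | Power, 60 vs 30 | Power, 24 vs 24 |
|---|---|---|---|
| Single point | 0.31 | 28% | 19% |
| Difference, opposite shift, r = 0.5 | 0.63 | 79% | 56% |
| Difference, opposite shift, r = 0.8 | 0.99 | 99% | 92% |
| Difference, upper only, r = 0.5 | 0.31 | 28% | 19% |
| Difference, upper only, r = 0.8 | 0.49 | 59% | 39% |
| Difference, upper only, r = 0.3 | 0.26 | 22% | 15% |

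With SD 1.0 °C, a single point has 20% and 14%. An opposite shift gives the difference 60% to 94% and 40% to 76% over r = 0.5 to 0.8.

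The reason is visible in the SD formula. The difference removes what the two points share, which is the child's overall skin temperature. It gains when r is above 0.5, or when the points move in opposite directions. With an upper-only shift and r below 0.5 it loses to the single point, as the last row shows. The 24 vs 24 column uses the raw SD and takes no credit for baseline.

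**Step 3: the same on change scores.** A simulation of 4,000 runs with 30 per group used a balanced shift of a × (1, 0.5, 0, −0.5, −1), point-level SD 0.3 °C and whole-back SD 0.3 to 0.8 °C, all assumed. At a = 0.2 °C the five-point average had about 5% power, that is, only the false-positive rate. The end-point tests had 14% to 44%, and a top-to-bottom contrast about 98%. At a = 0.5 °C the end-point tests reached about 60% to 99%, so per-point readings do register a large shift.

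**The case against.** **The measure is probably per point.** The markers, the tracing of individual points and the analysis section's reference to acupoint temperatures favour one t per acupoint. This stands. A reader might infer from the word for area that the outcome is wholly blind to redistribution, but that follows only on the less likely whole-area reading and for a shift that leaves the mean unchanged. On the likelier reading the outcome is insensitive and off target.

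**Temperature level is also a hypothesis.** The Introduction expects body temperature to change in TD, and the Discussion speaks of a temperature difference along the vessel. This stands too. Point temperatures answer part of the question and should not be reduced to description.

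**The gain rests on a favourable shape.** No section says that lower points cool as upper points warm. With an upper-only shift and r = 0.5 the difference has exactly the single point's power. This stands, and is why the gain must be given as a range.

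**Offsets are controlled.** Testing requirements fixes room temperature, limits humidity and requires a rest period, and randomisation balances general offsets in expectation. This weakens the false-positive route, above all for acupuncture against sham. It does not remove differences in overall skin temperature between children, and TD against healthy is not a randomised comparison.

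**The index could be left to an analysis plan, and the ANOVA wording might cover comparison across points.** A derived index could well appear elsewhere. But the article itself fixes the recorded variable, the points and the tests. A one-way ANOVA across points would neither treat the five readings as one child's nor compare evenness between groups.

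**Conclusion.** The point holds as a mismatch between the stated thermographic hypothesis and the measure and tests fixed for it. As written, the analysis can miss a redistribution of heat or attribute a general temperature difference to one. A reader might go further and infer that the trial cannot answer its thermography question at all. The article does not support that: if five readings exist, a large shift at the end points would show, and the level hypothesis is tested.

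With SD 0.8 °C and 60 against 30 children, a within-child difference has 79% to 99% power for an opposite 0.25 °C shift and 28% to 59% for an upper-only shift (r = 0.5 to 0.8), against 28% for a single point. All temperature SDs, correlations and shifts are assumptions. The mismatch itself needs none of them. Because thermography is secondary, this is a change that should be made and not a threat to the primary result.

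**What to change.** 1. In Testing process, state that t is recorded separately for each of the five points.
2. In Processing of infrared thermographic images, prespecify one within-child distribution index, for example the slope of temperature over the five points or Dazhui minus Yaoyangguan. State the top-to-bottom order (and, for a slope, the spacing) of the points, which the article does not give.
3. Compare the week-12 index, adjusted for its baseline value, between acupuncture and sham. Compare the baseline index between TD and healthy children.
4. Keep the point-temperature analyses alongside, because a change in skin temperature is also hypothesised.

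The points are already traced and the images saved, so the change costs only wording and one derived variable. Recruitment is described as ongoing, so the index can still be fixed before the database is locked. The downside is small: with r below 0.5 and an upper-only shift, the difference detects less than the single point does, a further reason to keep both analyses.
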